## Methods and analysis

### Trial design and flow chart

The design is a prospective parallel-group feasibility randomised controlled trial with single-blind assessment aiming to evaluate a novel targeted psychological intervention for distressing voices in early psychosis (AVATAR_VRSocial) in addition to usual care versus usual care alone. Assessments will be carried out at baseline (T1), at post-treatment at 3 months (T2) and at 6 months follow-up (T3). The assessments will be carried out by a researcher blinded to treatment allocation. This study will follow active consent. Participants will also be asked for consent at baseline (1) if they consent to be contacted for follow-ups to monitor changes and/or persistence of experiences and (2) if they consent to be contacted to take part in future research linked to the study and its results. Same procedure will be followed at each time point (T2, T3). Figure 1 depicts a summary of the study design.

**Figure 1 F1:**
[figure not shown]
Trial flow chart. TAU, treatment as usual.

### Randomisation and blinding

Eligible participants will be randomised after consenting to the study and completion of the baseline assessment. Allocation will follow 1:1 block randomisation, carried out by the study coordinator, using a validated online tool (https://www.sealedenvelope.com/). The study coordinator will be unblinded to treatment allocation and will inform participants of the outcome of the randomisation. Research workers who lead the baseline and follow-up assessments will be blinded to group allocation, but participants and therapists delivering the therapy will not be (it is not possible to blind them to whether the therapy is delivered or received). Participants will be reminded not to discuss their allocation with research workers when they meet them for the assessment. Breaches in blindness will be monitored and recorded and where operationally feasible assessments will be allocated to another (blinded) research worker.

### Participants

The study participants will be 40 people (aged 16 and above) with distressing voices and at early stages of psychosis (FEP 5 years). All research activities (including coordination of recruitment) will be based at the Mental Health Research and Treatment Centre (MHRCT), Ruhr-Universität Bochum, located in North Rhine-Westphalia region (Germany). The primary recruitment pathway will be referrals by medical professionals. Medical service centres, outpatient departments and private practitioners will be contacted for the purpose of recruitment and will act as patient identification centres. Potential participants whose mental health practitioner confirms that they experience distressing auditory hallucinations will be contacted by a member of their clinical team inviting them to learn more about the study. If a participant indicates interest, they will be contacted by a research worker who will confirm eligibility criteria and obtain consent to participate in the research. Potential participants will be offered the opportunity to discuss the study and at least 24 hours to decide whether to participate. The research worker will also assess capacity to provide consent to participate. Informative flyers will also be distributed in practices, which contain information for potential participants. Although the flyer asks participants to approach the research staff via their clinical team, previous experience shows that some will make a direct approach.^17 25^ Further self-referrals are possible because of interest generated through media/public engagement events or through the study website.

#### Inclusion criteria

Have current frequent and distressing voices (as measured by a score of at least one on each intensity of distress and frequency items of the Psychotic Symptoms Rating Scale—Auditory Hallucinations (PSYRATS-AH)), persisting for at least 6 months and speaking German.Confirmed diagnosis of affective or non-affective psychosis (F20-29, F32/33.3 and F31.2 in ICD-10^26^) on the medical records or through consultation with the study clinical team.With the onset of the first psychotic episode or first presentation to mental health services in the last five years.≥16 years old.Adequate German language skills to provide informed consent and engage with assessment and therapy sessions.To be able to give informed consent.

#### Exclusion criteria

Primary diagnosis of substance disorder, personality disorder or learning disability.AVHs secondary to an organic disorder.Currently participating or being confirmed to participate in another interventional study in which they are receiving an intervention which uses psychological therapy and focuses on voices.Profound visual/hearing impairment or insufficient comprehension of German to be able to engage in assessment or therapy.Currently experiencing an acute mental health crisis (ie, being at immediate and serious risk to self or others).

Participants have the right to withdraw from the study at any time for any reason. All efforts will be made to report reasons for withdrawal. If they wish to withdraw from the therapy only, all efforts will be made to obtain follow-up data. The chief investigator (CI) also has the right to withdraw patients from the study in the event of clinical contraindications: the intervention may be discontinued if the participant requests this or if the clinician judges, in consultation with the wider supervisory team, that the intervention is associated with a significant worsening of mental health. In this case, an adverse event (AE) form would also be completed. It is understood by all involved that an excessive rate of withdrawals can render the study uninterpretable; therefore, unnecessary withdrawal of participants should be avoided. Should a participant decide to withdraw from the study, all efforts will be made to report the reason for withdrawal as thoroughly as possible. Should a participant withdraw from therapy only but not from the study, efforts will be made to continue to obtain follow-up data and assess reasons for dropping out, with the permission of the patient.

### Assessments

The assessment of eligibility and confirmation of the inclusion and exclusion criteria will be supported by the use of the Structured Clinical Interview for DSM-V (SCID-5)^1^ and the distress and frequency items of the PSYRATS-AH.^18^

General demographic and relevant clinical data (including age, gender, ethnicity, sexual orientation, employment status, clinical diagnosis, current medication) will be obtained at baseline. Main clinical outcomes, including psychotic and affective symptoms, social anxiety and functioning, quality of life and self-esteem, will be assessed at all three time points (baseline assessment at 0 months, follow-up assessments at 3 months and 6 months).

Psychotic symptoms will be assessed using clinical interview measures, specifically the Psychiatric Symptom Rating Scales for both Auditory Hallucinations (PSYRATS-AH) and Delusions (PSYRATS-DEL),^18^ the Scales for the Assessment of Positive Symptoms^27^ and the Clinical Assessment Interview for Negative Symptoms.^28^ Characteristics of (Voice Characterisation Checklist)^29^ and beliefs about the voice (Beliefs about Voices Questionnaire Revised),^30^ Voice Power Differential Scale (VPDS),^31^ as well as related experiences and coping strategies (Experiencing voices outdoors)^32^ will further be assessed via self-report. Levels of anxiety around leaving the house as well as subsequent avoidance and coping will be assessed using the Oxford Cognitions and Defences Questionnaire^33^ and the Oxford Agoraphobic Avoidance Scale (O-AS).^34^

Depressive symptomatology will be obtained via the Depression, Anxiety and Stress Scale.^35^ Self-esteem will be measured using the Rosenberg Self-Esteem Scale.^36^ An overview of potential traumatic events will be obtained via the Mini-TALE.^37^ The EQ-5D- 5 L^38^ will quantify health-related quality of life.

Participants allocated to the AVATAR_VRSocial Therapy condition will further be asked to complete items regarding anxiety, perceived hostility, sense of presence and sensed presence at the end of each interaction with the avatar (adapted from refs.^39 40^). Following each VR session, participants will be asked to complete a short version of the State Social Paranoia Scale.^41^ Voice activity and content in the past week is monitored at the beginning of each session using select items of the PSYRATS-AH^18^ and the VPDS.^31^ After half of the sessions, participants will be asked to complete a measure of the therapeutic alliance (Working Alliance Inventory-Short Revised).^42^ Before starting the VR sessions, participants will be asked to complete the questionnaires related to social avoidance and social distress. After completion of the final session, participants will rate the acceptability and appropriateness of the therapy via the Acceptability of Intervention Measure and the Intervention Appropriateness Measure.^43^

A qualitative interview will be conducted with a subsample of consecutively recruited participants (n=10). This interview will take place once they have concluded their participation in all assessments in the trial. This interview will ask them for feedback on how they found the therapy, taking part in the trial and the technology/software involved. The interview will be conducted by a research worker or by a member of the Live Experience Advisory Panel with support from the research team.

Assessments and therapy sessions will be audio-recorded (after first establishing consent) to allow for assessment of adherence to the research protocol and assessment ratings. These will be stored securely on password-protected devices and then uploaded to the secure university server. Throughout the recruitment and research process, all efforts will be made to tailor to participants’ needs and preferences. Participants in the study will be reimbursed with a voucher worth €30 in online shopping portals for each baseline, post-therapy and follow-up assessments.

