**Methods and analysis:**

A randomised controlled feasibility trial will be conducted. 40 patients aged 18 or above who are at early stages of psychosis (first episode of psychosis in the last five years) and report distressing and interfering voices will be recruited. Participants will be randomised to receive either a novel, enhanced version of AVATAR therapy (AVATAR_VRSocial) in addition to usual care or usual care alone. Assessor-blinded assessments will be conducted at baseline, 3 months (post-intervention) and 6 months (follow­-up). Key therapeutic targets of AVATAR_VRSocial will be those established by the previous evidence of this approach (ie, power and control, self-esteem and future focus), while introducing exposure and management of distressing voices during social interactions. Analyses will focus on feasibility outcomes (recruitment, retention and completion rates) and preliminary estimates of intervention effects. Qualitative interviews will be carried out with participants allocated to AVATAR_VRSocial to gain a comprehensive understanding of participants’ views on the acceptability of the intervention and research procedures. Thematic analysis of the qualitative interviews will assess the acceptability of the intervention, trial procedures and the new VR technology and software involved.

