## Objectives

The primary objective is to assess the feasibility and acceptability of a targeted intervention to improve voices related distress, and social avoidance and distress in people at early stages of psychosis (FEP<5 years^24^). The second main research objective is to convene evidence on clinical outcomes to provide first estimates of efficacy of this enhanced version of AVATAR therapy (AVATAR_VRSocial) in a sample of German individuals with early psychosis, which can inform subsequent development and testing of the therapy. Table 1 summarises the objectives of the study and includes the associated feasibility markers and assessment measures.

**Table 1 T1:** Summary of objectives and related assessment measures

	Objectives	Measures
Primary	Assessing feasibility and acceptability of AVATAR_VR psychotherapy for people who experience distressing voice hearing	Number of patients referred to the study, consented, declined and retainedCompletion rates of each assessment measure and retention at follow-up assessmentsNumber and proportion of consenting participants within AVATAR_VRSocial condition who reach the point of therapy ‘exposure’ (attended at least five of nine therapy sessions)Number of adverse serious and non-serious adverse events in each condition
Secondary	Clinical information about preliminary estimates of clinical effectiveness of AVATAR_VRSocial in addition to treatment as usual vs treatment as usual alone in people in early stages of psychosis	Voice distress, frequency and severity of voices: PSYRATS-AHSocial anxiety and avoidance: O-AS, O-CDQOther voices measures: BAVQ-R; VPDS; Brief assessment of negative hallucinations when outsidePsychiatric symptoms: PSYRATS-DEL, DASS-21. CAINS, Rosenberg-Self-EsteemQuality of life: EQ-5D-5L
Qualitative	Assessing acceptability	AFIMFeedback from Qualitative Interview

AFIM, Acceptability and Feasibility of Intervention Measure; BAVQ-R, Beliefs About Voices Revised; CAINS, Clinical Assessment Interview for Negative Symptoms; DASS21, Depression Anxiety and Stress Scales; EQ-5D-5L, EuroQol BIOMED Research Programme; O-AS, Oxford—Agoraphobic Avoidance Scale; O-CDQ, Oxford Cognitions and Defences Questionnaire; PSYRATS-AH, Psychotic Symptoms Rating Scale—Auditory Hallucinations; PSYRATS-DEL, distress and frequency factors, and total scores on the delusional beliefs subscale of the Psychotic Symptoms Rating Scales; VPDS, Voice Power Differential Scale.

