The virtual scenarios are presented using a wireless head-mounted display (Pico 4) with a resolution of 2160 × 2160 pixels per eye, 122.16° diagonal field of view and mounted headphones. The personalised negative voice is exported from the AVATAR therapy platform to the VR scenarios. The therapist can trigger the negative voice at random intervals (determined by the system) or at his/her own demand depending on the person’s performance. As per the AVATAR therapy sessions, the three VR sessions consisted of three parts: the pre-VR discussion with the therapist, the immersive part using the VR headset (lasting approximately 10 min) and the post-VR debrief with the therapist. The person can request to stop the immersive experience at any point.

At the end of the final session, participants will be asked to complete a self-reported questionnaire to assess the acceptability of the intervention.^43^ The number of active sessions attended (ie, sessions involving active avatar dialogue or VR practice) by the participant will be measured to assess treatment adherence. Fidelity to the clinical manual will be assessed by the therapist by completing a session-by-session checklist of specified targets (these will also be used during training and ongoing supervision; see above). Each session will be audio-recorded with consent. Therapist competence, after completion of training, will be assessed by an expert in AVATAR therapy for general/clinical and avatar-specific skills using ratings adapted from the first AVATAR therapy trial and allowing for differing skill requirements for each level of therapy.

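### Acceptability is rated only after the final therapy session, so participants who stop early have no rating point and the scores are likely to over-represent completers

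*Protocol article*

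**What the plan says.** The Objectives section of the protocol article gives acceptability equal standing with feasibility: "The primary objective is to assess the feasibility and acceptability of a targeted intervention". In Table 1, the row headed as acceptability names two sources, a self-report acceptability measure and the qualitative interview.

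The timing of the self-report measure is stated twice. Under Assessments: "After completion of the final session, participants will rate the acceptability and appropriateness of the therapy". Under AVATAR_VRSocial: "At the end of the final session, participants will be asked to complete a self-reported questionnaire to assess the acceptability of the intervention". Neither place, nor any other, gives a rating point for someone who stops therapy before the end of the course. Table 2 puts that course at ten sessions: one assessment and avatar-creation session, six avatar dialogues and three VR sessions.

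The interview is for ten participants taken in order of recruitment. On its timing: "This interview will take place once they have concluded their participation in all assessments in the trial". The abstract restricts it to the therapy arm: "Qualitative interviews will be carried out with participants allocated to AVATAR_VRSocial to gain a comprehensive understanding of participants’ views on the acceptability". Its scope there takes in both the therapy and the way the trial was run.

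The article also covers people who leave. The text after the exclusion criteria deals with those who give up the sessions yet remain in the trial: "efforts will be made to continue to obtain follow-up data and assess reasons for dropping out, with the permission of the patient". Reasons for leaving the study are to be recorded as well, there and under Adverse events.

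**The concern.** A score collected only from people who reach the last session is conditioned on finishing. Finishing is itself one of the things that poor acceptability would reduce. Followed as written, the plan describes how acceptable the therapy was to those who stayed, and a reader may take this as its acceptability to those offered it.

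This matters most for the VR sessions, the new component. The article does not state the order of sessions outright. However, it describes VR as practising what was learnt in the dialogues, and it sets a measurement point before VR begins, so VR appears to come last. If so, a participant who stops before or during VR would give no acceptability score. The same participant could still count as having reached therapy exposure, which needs only five sessions out of nine.

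For people who leave the study altogether the gap is wider. On the natural reading of its timing, the interview misses them too, although it is also meant to inform on the acceptability of the trial procedures.

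**Working it through.** **Inputs from the article.** Planned arm size: 20 (Analysis). Rating point: after the final session only (Assessments; AVATAR_VRSocial). The article gives no acceptability rate, no cut-off for an acceptable score and no rate of reaching the final session, so there is no figure of the plan's own to reproduce. The 80% retention figure under Analysis concerns retention, and the 75% threshold there concerns treatment uptake. Neither is defined as reaching the last session, so neither is used as a completion rate.

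**Assumptions.** Let *c* be the share of the arm that gives a rating, *a*C the share of raters who approve, and *a*N the share of non-raters who would have approved. Take *a*C = 90% for illustration and vary *c* and *a*N.

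**Step 1: bounds with no assumption about non-raters.** The arm-level value is *c*·*a*C + (1 − *c*)·*a*N. Setting *a*N to 0 and then to 1 gives:

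- lower bound = *c*·*a*C
- upper bound = *c*·*a*C + (1 − *c*)

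With 16 of 20 rating, *c* = 0.80. The lower bound is 0.80 × 0.90 = 0.72 and the upper bound is 0.72 + 0.20 = 0.92. (90% of 16 is 14.4 people, so this is an illustration in proportions, not a count.)

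**Step 2: excess of the raters-only figure.** Excess = *a*C − [*c*·*a*C + (1 − *c*)·*a*N] = (1 − *c*)(*a*C − *a*N). At *c* = 0.80 and *a*N = 50% this is 0.20 × 0.40 = 8 points.

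| Share rating (of 20) | Bounds for whole arm | Excess, *a*N = 30% | Excess, *a*N = 50% | Excess, *a*N = 90% |
|---|---|---|---|---|
| 90% (18) | 81% to 91% | 6 points | 4 points | 0 |
| 80% (16) | 72% to 92% | 12 points | 8 points | 0 |
| 75% (15) | 67.5% to 92.5% | 15 points | 10 points | 0 |
| 50% (10) | 45% to 95% | 30 points | 20 points | 0 |

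**Step 3: who each source reaches.**

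- *Leaves therapy, stays in the study:* no stated rating point. Can complete the 3- and 6-month assessments, so remains eligible for interview. Reasons for stopping are sought.
- *Leaves the study:* no stated rating point, and missed by the interview. The reason for withdrawal is recorded where it can be obtained.
- *Completes the course and the assessments:* rating and possible interview.

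**The case against.** The strongest reply is that acceptability does not rest on these scores alone. Table 1 lists declines, retention, the proportion reaching exposure and adverse events under the joint feasibility and acceptability objective, and all of these count early leavers. The progression criteria that the article names are recruitment, retention and uptake; no acceptability score is tied to stop, amend or go. This stands, and it limits the consequences. It does not repair the scores: a behavioural marker or a recorded reason for leaving is not a rating and cannot be combined with completers' ratings.

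Four stronger readings are tempting, and the article does not support them.

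- *That acceptability is overstated.* The direction is likely but not established. The excess is zero if stoppers would rate the therapy as completers do, and the upper bounds in the table lie above 90%.
- *That everyone who drops out is excluded from the interview.* Sampling follows recruitment order, and timing follows assessments, not therapy. Therapy-only drop-outs stay eligible, though with no assured place.
- *That reasons for leaving will be missing.* The article commits to seeking them.
- *That the 75% uptake threshold implies 5 of 20 missing ratings.* Uptake is nowhere equated with reaching the final session.

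It may also be said that the final session could mean the last one attended, or that the full protocol covers early stopping. The first is possible, but the article's phrase about completing the final session reads as the end of the course, and one clarifying sentence would settle it. As to the second, the article does not simply leave the timing out: it states a rule, twice, and that rule selects completers.

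**Conclusion.** The point holds in a limited form. The acceptability and appropriateness ratings serve part of the primary objective and, as scheduled, come only from people who finish the course. They are likely, not certain, to look too favourable. People who leave the study are also missed by the interview; people who leave only the therapy are not.

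The size cannot be derived from the article. If 90% of raters approve and 16 of 20 rate, the arm-level value lies between 72% and 92%, and the raters-only figure exceeds it by 0 to 12 points for approval among non-raters between 90% and 30%. With only half the arm rating, the excess over the same range is 0 to 30 points. All of these rest on assumed rates. No sample-size figure and no named progression criterion depends on the point.

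**What to change.** - **Ratings.** Offer the existing measures to everyone allocated to AVATAR_VRSocial: at the final session or at the point of stopping, and otherwise around the 3-month assessment.
- **Who administers them.** The therapist, the unblinded study coordinator, or a remote form. A questionnaire given only to the therapy arm must not pass through the blinded research worker, as it would reveal allocation.
- **Reporting.** Give scores with the number rated out of all allocated (planned 20), separately for completers and early stoppers, since stoppers rate a shorter course.
- **Interviews.** Keep them after the last assessment that a participant attends. A research worker may conduct them, so interviewing at the moment of stopping could unblind later assessments. Make sure that the ten include therapy stoppers where they agree.

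The cost is a small amendment using existing instruments and the same number of interviews. Some stoppers will decline, and the scores may be less favourable. Recruitment was planned to end in April 2025 and data collection to run to September 2026. For participants already past these points, only the reporting of the denominator can be applied.
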